|             |                                                                                                                                                                                                                                                                                                                                                                                                                                                                                                                                                                                                                                                                                                                                                                                                                                                                                                                                                                                                                                                                                                                                                                                                                                                                                                                                                                                                                                                                                                                                                                                                                                                                                                                                                                                                                                                                                                                                                                                                                                                                                                                                                                                                                                                                                                                                                                                                                                                                                         |
|-------------|-----------------------------------------------------------------------------------------------------------------------------------------------------------------------------------------------------------------------------------------------------------------------------------------------------------------------------------------------------------------------------------------------------------------------------------------------------------------------------------------------------------------------------------------------------------------------------------------------------------------------------------------------------------------------------------------------------------------------------------------------------------------------------------------------------------------------------------------------------------------------------------------------------------------------------------------------------------------------------------------------------------------------------------------------------------------------------------------------------------------------------------------------------------------------------------------------------------------------------------------------------------------------------------------------------------------------------------------------------------------------------------------------------------------------------------------------------------------------------------------------------------------------------------------------------------------------------------------------------------------------------------------------------------------------------------------------------------------------------------------------------------------------------------------------------------------------------------------------------------------------------------------------------------------------------------------------------------------------------------------------------------------------------------------------------------------------------------------------------------------------------------------------------------------------------------------------------------------------------------------------------------------------------------------------------------------------------------------------------------------------------------------------------------------------------------------------------------------------------------------|
|             | 
considered, including patients regardless to the degree to which they have been exposed to the intervention (as this is a pragmatic trial). Outcomes will be estimated for the whole dataset. 95% confidence intervals will be reported.
 
The description of the baseline characteristics including the self-rated health status (SRH), the primary and secondary endpoints will be presented for all patients and stratified by arm and other subgroups (eg.: age group, etc.). Comparisons between arms will be performed using the chi-square/Fisher test for categorical variables and/or t-test/ANOVA or nonparametric Wilcoxon/Kruskal-Wallis test for continuous variables. Significance level of 5% will be adopted.
 
The primary outcome of the study will be calculated using a GLM model for binary outcome with an identity link function to estimate the risk difference or the difference between Intervention and Control groups in the proportion of patients who discontinued or decreased PPI dosage at 6 months of follow up. Results will be adjusted for baseline covariates. Relative risk will be calculated as well as the number needed to treat (NNT) – the inverse of the difference in absolute rate of discontinuation between the intervention and control groups. Analysis will also be conducted at 3 months of follow up. Significance level adopted is <math>\alpha = 0.05</math>.
 
Regarding secondary outcomes, descriptive statistics will be calculated for all patients and reported with respect to each time point. For each outcome, adequate GLM models will be used to compare groups with respect to therapeutic outcomes (PPI specific and other medication), Quality of life (EQ-5D-5L), BMQ specific applied to PPI, Adherence (MAT) and healthcare resource utilization. Changes over time points will be evaluated.
 
Patients' level of satisfaction and process outcomes will be analyzed only for the intervention arm. Process outcomes will be used to assess the fidelity and quality of the collaborative intervention.
 
Time to PPI discontinuation will be assessed through Kaplan-Meier (KM) estimator. Results will be stratified by group and KM curves will be presented. Log-rank test will be computed to compare results between cohort subgroups. In alternative, multivariate Cox Proportional Hazards models will be used if groups are unbalanced and hazard ratios computed.
 |
| Sample Size | 
Our study will be conducted to detect a minimal 20% increase in the rate of discontinuation of inappropriate medication use caused by the intervention compared with the usual care. Assuming an alpha of 5%, 90% power and an allocation ratio of 1:1, we estimate that the minimum total sample size to detect differences between intervention and Control group is 178 patients (89 patients per group).
 
Considering a 20% lost to follow-up, then a total of 222 patients (111 per group) will be needed. The sample size was calculated using the software G*Power version 3.1.9.6.
                                                                                                                                                                                                                                                                                                                                                                                                                                                                                                                                                                                                                                                                                                                                                                                                                                                                                                                                                                                                                                                                                                                                                                                                                                                                                                                                                                                                                                                                                                                                                                                                                                                                                                                                                                                                                                                                                 |

|                     |                                                                                                                                                                                                                                                                                                                                                                                                                                                                          |
|---------------------|--------------------------------------------------------------------------------------------------------------------------------------------------------------------------------------------------------------------------------------------------------------------------------------------------------------------------------------------------------------------------------------------------------------------------------------------------------------------------|
| Economic Evaluation | 
An Economic Evaluation will be conducted alongside the non-randomized controlled trial, including the collection of costs and outcome data alongside the trial.
 
The economic evaluation will adopt a National Health Service perspective as base case, including all health care resource use data, but also a broader perspective in scenario analyses, including out-of-pocket expenses. The time horizon in the base-case analysis will be of 6 months.
 |
| Ethics/Legal        | 
This study will comply with all requirements stated in the Portuguese Law of Clinical Investigation, the Declaration of Helsinki, and any other applicable local regulations.
                                                                                                                                                                                                                                                                                     |

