| Outcomes             | 
The outcomes are measured at patient level.
 
The primary outcome is the successful deprescription – discontinuation or decreased dose of PPI, defined as a statistically significant reduction in medication burden between the intervention and control group between baseline, 3 and 6-month follow-up.
 
Secondary outcomes are:
 
 
• Time to PPI discontinuation considered the time until complete withdrawal since recruitment; Change in medication burden that is, the mean number of regular medications patient take and proportion of patients on polypharmacy (patients with 5 or more medicines) assessed at baseline and 6-month follow-up;
 
• Change in Drug-drug interactions, assessed at baseline and 6-month follow-up;
 
• Change in Adverse drug events, that is, the absolute and relative counts of self-reported adverse drug events and type of events (e.g., needed professional support) experienced by patients, assessed at baseline and 6-month follow-up;
 
• Change in Patient Reported Outcomes Measures (PROMs) assessed at baseline and 6-month follow-up: Quality of life related to health, will be evaluated using the five-level version of the European Quality of Life-5 Dimensions questionnaire (EQ-5D-5L instrument); Self-reported adherence using a 7 items Measure Treatment Adherence questionnaire (MTA); and Patients' beliefs about inappropriate medicines, assessed by the beliefs about medicines questionnaire (BMQ-specific) this assessed at baseline and 3 months;
 
• Satisfaction with the collaborative intervention (general and health professional related), at 6-month follow-up in the intervention group.
 
• Process outcomes, to assess the fidelity and quality of the collaborative intervention.
 
 |

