#### Change in other Medication-related parameters | Profile and Safety outcomes.

- Medication burden that is, the mean number of regular medications patient take and proportion of patients on polypharmacy (patients with 5 or more medicines as commonly accepted definition (89)), assessed at baseline and 6-month follow-up.
- Drug-drug interactions (DDIs), that is, the absolute and relative counts of drug-drug interactions and by degree of severity, patients with any drug-drug interaction and with severe interactions. Most frequent severe drug-drug combinations will also be reported. Drug-drug interactions will be assessed by sifarma® software interaction alert system considering all medications taken, assessed at baseline and 6-month follow-up. Moderate and serious DDIs will be checked by the researchers using the Sifarma® software safety module. This module is an Electronic Information platform on medicines integrated on the Sifarma® dispense software, with updated information regarding clinically relevant Drug-Drug interactions (DDIs). This platform is powered with the summary of medicine characteristics (RCM) and other information sources as Stokley's Drug Interactions and Lexicomp. DDIs are classified according with 2 types of severity: a) Moderate DDI - Drug associations which benefit from (or for which it is recommended) monitoring, dose adjustment or any other form of management; b) Severe DDI - potential life-threatening and/or requiring medical intervention to minimize or prevent serious adverse effects; drugs are contraindicated for concurrent use. The software

displays an automatic alert regarding the DDIs identified and provide additional information regarding the mechanism of interaction.

- Adverse drug events, that is, the absolute and relative counts of self-reported adverse drug events and type of events (e.g., needed professional support) experienced by patients, assessed at baseline and 6-month follow-up.

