#### Change in Patient Reported Outcomes Measures (PROMs):

- Quality of life related to health, will be evaluated using the five-level version of the European Quality of Life-5 Dimensions questionnaire (EQ-5D-5L instrument) (90,91), assessed at baseline and 6-month follow-up; EQ-5D-5L scores will be computed for each patient.
- Patients' beliefs about inappropriate medicines, assessed by the beliefs about medicines questionnaire (BMQ-specific)(92) applied to PPI; assessed at baseline and 3-month follow-up. It comprises two sub-scales: the specific necessity scale (SNS) assessing patients' views on their personal need for their medication and the specific concerns scale (SCS) assessing patients concerns towards their medication.
- Adherence using a self-reported 7-item Measure Treatment Adherence (MTA) tool (93), applied at baseline and 6-month follow-up. The MTA, a psychometric tool derived from Morisky et al, evaluates the individuals' behaviour in relation to the daily use of medication. Each item is scored from 1 (always) to 6 (never). Points are summed and divided by the total number of items. Higher scores indicate higher self-reported adherence. Patients with values of 5 and 6 are considered adherents. We select this method to measure multiple medication adherence because is simple to apply and was validated for the Portuguese Population in 2001, with a reported Cronbach's alpha of 0.74.

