#### **Secondary outcomes**

Descriptive statistics will be calculated for all patients and reported with respect to each time point. Adequate GLM models will be used to compare groups with respect to clinic characteristics, therapeutic outcomes (PPI specific and other medication), Quality of life (EQ-5D-5L), BMQ specific applied to PPI, Adherence (MTA) and healthcare resource utilization. Changes over time points will be evaluated.

Patients' level of satisfaction and process outcomes will be analyzed only for the intervention arm. Process outcomes will be used to assess the fidelity and quality of the collaborative intervention.

Time to PPI discontinuation will be accessed through Kaplan-Meier (KM) estimator. Results will be stratified by group and KM curves will be presented. Log-rank test will be computed to compare results between cohort subgroups. If groups are unbalanced with respect to potential confounders, multivariate Cox Proportional Hazards models will be used instead. Univariate and multivariate hazard ratios (HR) will be computed, and Wald's 95% CI presented. Patients will be censored in the survival

analysis if they were lost to follow-up (subjects who could not be reached by telephone interview, or the primary outcome could not be computed or withdrew consent), hospitalized or died.

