#### **6.17.4.2. Health-related quality of Life**

The Health-Related Quality of Life (HRQoL) will be assessed using the EQ-5D-5L questionnaire applied at baseline and 6-month follow-up. The EQ-5D-5L is a generic preference-based measure of health state that covers five dimensions (mobility, self-care, usual activities, pain/discomfort, and anxiety/depression) that can be rated according to five levels of severity to define unique health states. The five-level version has showed increased reliability, sensitivity (discriminatory power) and feasibility compared to the previous three-level instrument. Participants are classified into one of 3125 health states, each associated with a score that can be used to calculate quality adjusted life years (QALYs) (103)

HRQoL weights for these health states have been previously elicited for the Portuguese population by Ferreira et al. (91,104). A score of 1 represents perfect health and a score of 0 represents death. The EQ-5D scores will be used to estimate patient-specific QALYs using the area under the curve method (105).

Mean QALYs measured by EQ-5D will be estimated using regression analysis to control for patients' covariates, including baseline EQ-5D score, (106) and will be used as a secondary outcome measure in the economic analysis.

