#### **6.17.5. Cost and cost-effectiveness analysis**

Costs will be modelled with the most appropriate distribution for data. All analyses will be adjusted for pre-specified baseline characteristics, plus baseline costs.

Cost-effectiveness will be explored in terms of the primary outcome measure (reduction in PPI use) and QALYs and, will be assessed through the calculation of incremental cost-effectiveness ratios (ICER) – the additional cost of one intervention compared with another divided by the additional effects – using the net benefit approach (107). Cost-effectiveness acceptability curves will be presented by plotting the probability of the intervention being cost-effective for a range of possible values of willingness to pay for unit improvements in outcome (108). These curves are a recommended decision-making approach to dealing with the uncertainty that exists around the estimates of expected costs and expected effects associated with the interventions under investigation.

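### Secondary outcomes are framed as changes, and baseline adjustment of their comparison is promised only if the arms turn out unbalanced; each outcome's own baseline value should always be in its model

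*Protocol*

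**What the plan says.** **Outcome definitions.** The Protocol Summary lists, for example, "Change in Drug-drug interactions, assessed at baseline and 6-month follow-up". Section 6.8 groups the secondary outcomes under "Change in other Medication-related parameters | Profile and Safety outcomes" (medication burden and polypharmacy, drug-drug interactions, adverse drug events) and "Change in Patient Reported Outcomes Measures (PROMs" (EQ-5D-5L, BMQ-specific, MTA). Tables 4 and 5 collect all of these at baseline and again at follow-up: 3 months for BMQ, 6 months for the others.

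**Secondary analysis.** The Protocol Summary states "For each outcome, adequate GLM models will be used to compare groups with respect to therapeutic outcomes (PPI specific and other medication"). Section 6.15.2 repeats it as "Adequate GLM models will be used to compare groups with respect to clinic characteristics, therapeutic outcomes" and adds "Changes over time points will be evaluated". Neither place says whether the response is the change or the follow-up value, and neither names a link or a covariate.

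**Adjustment elsewhere.**
- Section 6.15.2, primary outcome: results are adjusted for baseline covariates, without condition.
- Section 7, recruitment and selection bias: adjusted and unadjusted estimates of both primary and secondary outcomes are produced if confounders are unbalanced. The examples are age, sex, health status, baseline beliefs and medicine burden.
- Section 6.17.4.2: mean QALYs are estimated by regression on "covariates, including baseline EQ-5D score".
- Section 6.17.5: "All analyses will be adjusted for pre-specified baseline characteristics, plus baseline costs".

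**The concern.** The arms come from different municipalities and patients are not randomised (section 5). Section 6.1 matched control sites on purchasing power, ageing, illiteracy, unit type and PPI prescribing volume, not on the baseline level of any secondary outcome other than through those proxies. Baseline differences in quality of life, adherence, interactions or adverse events are therefore to be expected.

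The only adjustment rule that reaches the secondary outcomes is the one in section 7. It is triggered by the data, gives no threshold for imbalance, and does not say which of the two estimates is the main one. Baseline EQ-5D, MTA, interactions, adverse events and resource use are not among its named examples. Under that rule, the main estimate for a secondary outcome could be chosen after the baseline table has been seen. Where no adjustment is triggered, precision that the collected baseline values would give is lost. The protocol already applies the better practice to QALYs and costs.

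**Working it through.** **1. The rules side by side**

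| Quantity | Baseline adjustment | Own baseline in the model |
|---|---|---|
| Primary outcome (6.15.2) | always | not applicable (all are PPI users at entry) |
| Primary outcome (7) | if unbalanced | not applicable |
| BMQ, medicine burden (6.15.2 with 7) | if unbalanced | named as an example |
| EQ-5D, MTA, interactions, adverse events, resource use (6.15.2 with 7) | if unbalanced | not named |
| QALYs (6.17.4.2) | always | baseline EQ-5D |
| Costs (6.17.5) | always | baseline costs |

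Section 7 therefore differs from section 6.15.2 even for the primary outcome, and the own-baseline rule is applied only in the economic part.

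**2. Sample size used for the precision check**

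Section 6.11 gives 89 per group (10% v 30%, two-sided Fisher's exact test, 5%, 90% power). Exact enumeration gives power 0.90174 at 89 per group, against the stated 0.9017447, and 0.8977 at 88. The figure of 89 is reproduced and used below. The protocol states no figure for any secondary outcome.

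**3. Precision for continuous outcomes**

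Assumptions: common SD of 1 and baseline-to-follow-up correlation r between 0.3 and 0.9. The protocol gives neither.

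- Variance per patient: change score 2(1−r); baseline-adjusted 1−r²; unadjusted follow-up value 1.
- Ratio of change to adjusted: 2(1−r)/(1−r²) = 2/(1+r).
- Detectable difference at 90% power: (1.960 + 1.282) × √(2/89) × √variance = 0.486 × √variance.

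| r | Change / adjusted variance | Detectable difference, change (SD) | Detectable difference, adjusted (SD) |
|---|---|---|---|
| 0.3 | 2/1.3 = 1.54 | 0.575 | 0.464 |
| 0.5 | 2/1.5 = 1.33 | 0.486 | 0.421 |
| 0.7 | 2/1.7 = 1.18 | 0.376 | 0.347 |
| 0.9 | 2/1.9 = 1.05 | 0.217 | 0.212 |

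For an assumed effect of 0.4 SD, power rises from 0.76 (change) to 0.87 (adjusted) at r = 0.5, and from 0.93 to 0.96 at r = 0.7. If the unadjusted follow-up value were compared instead, its variance relative to the adjusted model is 1/(1−r²): 1.33 at r = 0.5 and 1.96 at r = 0.7.

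Adjustment costs little when the arms differ at baseline. With an assumed gap of 0.3 SD, the squared correlation of arm with baseline is 0.0225/1.0225 = 0.022, so the variance inflation is 1/(1−0.022) = 1.02.

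**4. Bias from a baseline gap**

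Assume a gap d = 0.3 SD and no intervention effect.

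- If both arms regress to a common mean, the change score is off by −(1−r)d and the adjusted model by 0. For r = 0.3, 0.5 and 0.7 the change score is off by −0.21, −0.15 and −0.09 SD.
- If the gap is a stable difference between populations, the change score is off by 0 and the adjusted model by +(1−r)d: +0.21, +0.15 and +0.09 SD.

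The direction of advantage depends on why the arms differ, which the data cannot fully settle.

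**The case against.** **The models are only unspecified.** The protocol says a statistical analysis plan will be drafted before any analysis. The response, link and covariates of secondary models are ordinary content for that plan, and nothing in the protocol excludes the baseline value. This stands: silence in section 6.15.2 is not in itself an error, and a reader should not infer that own baselines are ruled out. It does not cover section 7, where the protocol does state a rule, and that rule is conditional.

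**Stronger readings that the text does not support.**
- A reader might infer that adjustment is planned for the primary outcome only. Section 7 expressly extends adjusted estimates to the secondary outcomes, though conditionally.
- A reader might infer that the planned GLMs cannot handle yes/no outcomes and counts, because a patient-level change in them can be negative. The protocol does not fix the patient-level change as the response. A binomial or Poisson model of the follow-up value fits its wording.
- A reader might infer that EQ-5D is analysed in two contradictory ways. QALYs over 6 months and the EQ-5D score are different quantities. The point is only that the same principle is applied to one and not stated for the other.

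**Baseline adjustment is not a cure in a non-randomised design.** This also stands. If the gap is a stable population difference, the change score is the unbiased one, as step 4 of the working shows. The case for always adjusting therefore rests on precision and on fixing the analysis in advance, not on a general claim of less bias.

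**Conclusion.** The point holds in a limited form. The protocol frames its secondary outcomes as changes, names no baseline adjustment in their models, and makes adjustment depend on observed imbalance. That rule is weak for non-randomised arms, and it is out of line with section 6.15.2 for the primary outcome and section 6.17 for QALYs and costs.

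For continuous outcomes, an unadjusted change score would have about 1.05 to 1.54 times the variance of a baseline-adjusted comparison, for r from 0.9 to 0.3. The loss is small if r is high. These figures rest on assumed correlations, equal SDs and 89 analysed patients per arm, and they apply only if the analysis is in fact an unadjusted change score. The bias consequence cannot be signed from the documents. The primary outcome's sample size is unaffected. This is a worthwhile and nearly free improvement, not a flaw that undermines the trial.

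**What to change.** In the Statistical Methods row of the Protocol Summary and in section 6.15.2, state the following:

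- Each secondary outcome measured at baseline is compared between arms on its follow-up value: 3 months for BMQ, 6 months otherwise, including healthcare resource use.
- The model always contains that outcome's own baseline value plus the pre-specified confounders.
- The link suits the outcome type, for example identity for scores, log for counts and a binomial model for yes/no outcomes.
- The unadjusted comparison of changes is reported as a sensitivity analysis, because the arms are not randomised.

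Reword section 7 so that the balance table is descriptive and no longer decides whether adjusted estimates are produced. This also removes its conflict with the unconditional adjustment of the primary outcome.

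The cost is a few sentences of protocol or analysis-plan wording and no new data, since Tables 4 and 5 already schedule the baseline values. Patients without a baseline value need imputation or drop out of that model. A change score would lose them too, so this is an added loss only against a comparison of follow-up values alone.
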